## Eligibility criteria {10}

### Participant inclusion and exclusion criteria

To enroll in the study, school administrators will be invited to sign a memorandum of understanding (MoU) indicating their willingness to participate. The students from the participating schools will be informed about the study by a contact person from the school. Then, the project team will organize a session with students one week before implementation starts to describe the program in detail. All students aged 13 to 20 who express interest in joining the program will be eligible for the study, with no additional exclusion criteria applied.

The Shamiri intervention will be delivered by trained group facilitators, all lay providers with at least a high school degree, who will each lead the intervention for a group of 10 to 15 adolescents. Lay providers will be included if they live near Makueni or Machakos counties, are between the ages of 18 and 24, and graduated from a Kenyan secondary school. Applicants who meet these criteria will participate in 30-min interviews and will be selected based on their counseling or group facilitation skills and knowledge of common issues faced by Kenyan secondary school students. The recruitment and training of lay providers will closely mirror the procedures employed in previous trials of the Shamiri Intervention [17].

Recruiting local peers as lay providers has several advantages; the local lay providers are connected and well-versed in the culture of our target population and will thus be able to relate well to the target group. Furthermore, if the intervention again proves to be successful, one of the most efficient and cost-effective ways of scaling up will be through local lay providers.

### Who will take informed consent? {26a}

Local customs and policies authorize school administrations to decide on any activity (including research) involving students. Therefore, the school heads will represent guardians and parents in receiving information about the study and may contact parents and guardians according to local customs [22]. The school heads will be given the opportunity to ask questions concerning the study and provide consent for all students by enrolling their school into the program by signing an MoU. The school administrators will be given an option to contact the students’ parents and guardians at home if they deem it appropriate.

Also, before sessions begin, interested students will be provided with more information about the study and an opportunity to ask questions. Students will be informed that participating in the study is voluntary and that they can opt out of the study at any time. Interested students will then be asked to provide consent, or assent for minors, prior to enrollment in the study.

### Additional consent provisions for collection and use of participant data and biological specimens {26b}

N/A. We will only collect the data mentioned in the “Outcomes {12}” section, and no biological specimens will be collected in this study.

## Interventions

### Explanation for the choice of comparators {6b}

The primary objective of this trial is to compare a centralized vs decentralized approach to scaling, assessing the comparative effectiveness of each approach. To achieve this, the Shamiri-Institute-delivered intervention (centralized) will be compared against the Shamiri Intervention delivered by the implementing partner (decentralized). A treatment as usual control group is included to provide a practical reference point from which the intervention’s efficacy for both implementors will be estimated relative to what school-going adolescents would typically receive.

## Intervention description {11a}

### Shamiri intervention

The Shamiri intervention entails four weekly one-hour group sessions. The first two sessions are centered around growth mindset. The third and fourth sessions focus on gratitude and value affirmation, respectively. Sample intervention protocols can be found in supplementary materials.

#### Session 1: Growth mindset

This first session will introduce adolescents to the concept of having a growth mindset [23, 24] which is defined as the belief that intelligence, abilities, and talents can be developed through hard work, persistence, and dedication. Adolescents will discuss the human capacity for personal improvement and growth in various areas of their lives including emotional, social, and academic.

Additionally, students will be introduced to the concept of neuroplasticity, the idea that the human brain grows and makes new connections by learning and practicing new skills, through a short script. As part of the session, adolescents will read growth testimonials from local Kenyan peers that cover personal growth in various areas including social life, personality, academic performance, happiness, and views. At the end of the first session, students will receive an assignment that asks them to reflect on a challenge they have faced, strategies they used to address it, and reflect on how the challenge influenced their personal growth. This take-home assignment will be discussed during the following week.

#### Session 2: Growth mindset

The second session will entail discussing the take-home assignment, a letter-writing exercise, and completing a problem-solving practice task. The session will begin with the participants sharing feedback on the assignments they completed during the previous week. The students will then engage in a letter-writing exercise, where they will write a letter to a friend explaining what they have learned so far, including problem-solving, effective strategies, growth mindset, and neuroplasticity.

At the end of session two, the study participants will be given an assignment focused on problem-solving. They will be asked to identify one problem they are facing at that time and apply the problem-solving skills they learned to come up with a solution. They will be encouraged to implement one or two solutions during that week.

#### Session 3: Gratitude

During the third session, participants will be introduced to gratitude and its benefits [20–22]. They will have the opportunity to discuss this concept and mention the people and things in their lives for which they are grateful. The participants will then write a “gratitude letter” to a person who has positively impacted their life.

At the conclusion of this session, participants will be given an assignment to write down three positive things from their lives. They will be instructed to carry out this exercise daily and write a brief reflection for each item listed in the daily exercise.

#### Session 4: Value affirmation

The fourth session will be focused on value affirmation [25, 26]. In the Kenyan context, the term “virtue” is often used interchangeably with “value” [13, 20]. The lay provider will begin the session by leading a discussion on the concept of values/virtues and why they are important in shaping purpose and behavior.

From a long list of values/virtues, the group members will be asked to pick the ones that are most meaningful to them. They will then be asked to write on the importance of the selected value/virtue, how they have demonstrated it in the past, and how they will incorporate it in the future and connect it to their personal goals. At the end of this session, no additional assignments will be given to the participants.

### Treatment as usual control

Participants who are assigned to receive treatment as usual will receive the standard care that is offered at their respective schools [27]. Schools in Kenya offer different forms of care to students in need ranging from guidance and counseling from teacher to community activities and support. Besides this, students in the TAU control group will be allowed to approach the study team members at any time with questions and concerns. Students who need urgent support will be attended to according to our emergency protocol and will not be excluded from participating unless it is deemed necessary for their safety and wellbeing.

### Criteria for discontinuing or modifying allocated interventions {11b}

A participant may discontinue their assigned intervention if they decide to withdraw from the intervention, exhibit behavior so disruptive that it harms the other participant’s ability to participate even after requests to change their behavior or if the study team determines that it is necessary for the participant’s safety and well-being for them to cease participating. We expect some students to voluntarily choose to leave the study, but we expect there will be minimal or no need to forcibly remove any participants. If a participant misses any session, they will still be allowed to participate in the study. Participants will be encouraged to maintain the allocated groups throughout the study with no modifications or discontinuations.

Once the trial commences, we do not intend to modify the assigned interventions. However, prior to the start of implementation, minor adjustments may be made to the intervention protocols (e.g., phrasing edits) based on feedback from trainees or other stakeholders. The final intervention protocols will be made available in published manuscripts.

### Strategies to improve adherence to interventions {11c}

We will employ several strategies to encourage and evaluate compliance with intervention procedures. The first involves comprehensive training for all lay providers. They will undergo didactic training and engage in roleplays to effectively administer the intervention. They will also be instructed on the use of the emergency protocols when necessary and will be instructed in and expected to follow general trial guidelines, such as maintaining participant confidentiality. This training will be supplemented by tailored assessments such as a post-training readiness survey and real-time role play evaluation and feedback.

Second, we will ensure adherence through supervision. This will include both weekly in-person meetings and daily supervision by trained supervisors to verify compliance with the intervention protocols. All supervisors will have at least a bachelor’s degree in psychology and prior counseling experience. They will undertake a seven-week training on ethical considerations, the Shamiri Intervention, and trial protocols. Furthermore, a clinical network consisting of PhD-level mental health experts will oversee these supervisors.

The final approach is the measurement of adherence to the protocols during intervention implementation. This will be accomplished by enlisting independent raters to assess a randomly selected portion (10%) of session recordings on fidelity and performance, using a method similar to previous trials [8, 13, 20]. Each recording will be evaluated by two independent raters, after training on the use of the fidelity rubric, and their level of agreement will be assessed using Gwet’s AC2 [28, 29] for ordinal rating scales.

### Relevant concomitant care permitted or prohibited during the trial {11d}

During the trial, participants will have the freedom to seek alternative forms of care or use medication. Those in the control condition will be encouraged and referred to utilize the standard mental health services provided by their respective schools. However, as mentioned in the “Adverse event reporting and harms {22}” section, participants identified by the study team as presenting significant risk of self-harm or harm to others will be strongly encouraged to seek professional mental health assistance from a provider from the network of mental health experts affiliated with the study team. If a student requires ongoing post-trial care, arrangements will be made in coordination with the school administrators. Unless the principal investigator (PI) deems it necessary for the participants’ well-being, students referred to external care will not be excluded from the sample or removed from the groups.

### Provisions for post-trial care {30}

As explained in the “Adverse event reporting and harms {22}” section, the study team will periodically evaluate the level of risk of participants who exhibit potential risk of self-harm or harm to others using the emergency protocol (refer to the supplementary materials for the complete emergency protocol). If deemed necessary by the study team, these students will be referred to the clinical network, the third tier of the Anansi caregiving model, for individual support both during or after the trial. We do not anticipate any harm resulting from participants’ involvement in the trial, and as a result, we have no provisions for compensation in case of harm.

## Outcomes {12}

### Primary outcomes

#### Patient Health Questionnaire-8 (PHQ_8)

We will use the PHQ-8 to assess adolescents depression symptoms. PHQ-8 is a shortened version of PHQ-9 that excludes the ninth suicidal ideation item at the advice of Kenyan stakeholders [30, 31]. PHQ-9 and PH-8 measures are highly correlated, and the same cutoffs can be used to assess depression severity. We have previously validated PHQ_8 among Kenyan adolescents and it showed good internal consistency (Cronbach’s alpha = 0.78) [8, 31–33].

#### Generalized Anxiety Disorder-7 (GAD_7)

The GAD-7 is a globally used measure for screening generalized anxiety disorder in both adolescents and adults. GAD-7 has been validated for use in Kenyan adolescents (Cronbach’s alpha = 0.82) [8, 32, 33].

#### Multidimensional Scale of Perceived Social Support (MSPSS)

The MSPSS is designed to assess satisfaction with social support. It is composed of three subscales: the “friends” subscale, the “family” subscale, and the “significant others” subscale. The MSPSS has demonstrated adequate internal consistency in Kenyan adolescents (Cronbach’s alpha = 0.86) [12, 32, 33]. In this study, we will use the friends and family subscales to evaluate adolescents perceived social support.

#### Academic performance

Data on academic performance will be collected for the school term preceding, during, and after study implementation. We will measure students’ academic performance by calculating their average grade across all subjects each semester. Grades will be standardized using a method utilized in previous trials [12] to allow comparison between schools and across different grade levels.

#### Short Warwick-Edinburgh Measure of Mental Well-Being Scale (SWEMWBS)

The SWEMWBS is a shortened version of Warwick-Edinburgh Measure of Mental Well-Being Scale (WEMBS). Unlike the WEMBS, which has 14 items, SWEMBS has 7 items, and it is used to assess an individual’s general mental well-being. This measure has been used in past studies [8, 13, 32] in Kenya and has demonstrated good psychometric properties (Cronbach’s alpha = 0.70) [34].

### Secondary outcomes

#### Perceived Control Scale (PCS) Academics

The PCS Academics consists of six items related to beliefs about personal control, specifically the belief that one can obtain desired outcomes and avoid undesired outcomes in school through effort. PCS has demonstrated adequate internal consistency among Kenyan adolescents (Cronbach’s alpha = 0.78) [32, 33].

#### The Gratitude Questionnaire-6 (GQ_6)

The GQ_6 is a six-item questionnaire that assesses individual experiences of appreciation and gratitude in daily life. The GQ has been validated in Chinese and Taiwanese populations with Cronbach’s alpha ranging from 0.76 to 0.84 [35, 36] for the six items. We have used GQ_6 in our past studies with Kenyan adolescents, and it showed good internal consistency (Cronbach’s alpha = 0.79) [32]. We will use it to assess participant’s gratitude and appreciation experiences in this trial.

#### School Engagement Scale (SES)

We will use SES to assess cognitive, emotional, and behavioral characteristics of students’ school engagement. This scale has been validated in Chicago, India, Turkey, and Russia, showing acceptable internal consistency with a Cronbach’s alpha of 0.72–0.86 [37–40]. Additionally, the SES scale has also been used in South Africa to predict school engagement and it showed excellent internal consistency (Cronbach’s alpha = 0.92) [41]. Additionally, the SES scale has also been used in South Africa to predict school engagement and it showed excellent internal consistency (Cronbach’s alpha = 0.92) [41].

#### Demographics

We will collect socio-demographic information from the participants, including age, form, gender, county, socio-economic status, family, home, and religion/spirituality using a self-report questionnaire (see supplementary materials).

### Participant timeline {13}

The study will be implemented between May and August 2023. During this period, data will be collected within specified periods: at baseline (0 weeks into the study), midpoint (2 weeks into the study), endpoint (4 weeks into the study), and 1-month follow-up (8 weeks into the study) as shown in Table 1.

**Table 1 Tab1:**
[figure not shown]
Schedule for enrollment, interventions, and outcomes for the three-arm trial for scaling Anansi model

### Sample size {14}

We used the *simr* package in R to estimate the sample size needed for this trial. We used the lowest standardized effect size between the intervention and control we observed in a prior study [8] as our target effects, which was 0.22. Power simulations revealed that to detect an effect size of at least 0.22 at any time point with a significance level of *α* = 0.05 and a power of at least 80%, an effective sample size (i.e., including attrition of 40%) of 1554 participants is required. We expect up to 30% attrition at the midpoint and endpoint and up to 40% by follow-up based on our past trial [8], which is high. We rounded this up to 1600 participants required at baseline. For more details on our sample size determination and power analysis procedure, please see the supplementary materials.

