## Discussion

In LMICs such as Kenya, the mental health treatment gap is estimated to be as high as 85%. Addressing this treatment gap has become an urgent global health priority, for which interventions need to be developed and implemented. Recent evidence highlights the potential of brief, low-touch interventions that focus on overall human functioning rather than solely targeting psychopathology [11, 46]. Within this context, the Shamiri intervention has been developed as a school-based and a lay-provider delivered intervention targeting anxiety and depression symptoms in adolescents. Previous RCTs of the Shamiri intervention have demonstrated its effectiveness in reducing depression and anxiety symptoms, with effects comparable to those of traditional psychotherapy [8].

In addition to reaching adolescents that otherwise would not have access to mental healthcare, this type of intervention also has the potential to reduce stigma as students are treated equally in a school-based group setting regardless of their symptom levels and the intervention may eliminate the need to travel to a clinical setting for treatment. However, to reach as many youths as possible, the Shamiri intervention needs scaling. It is still not known whether the effectiveness of the intervention is maintained when scaling up the intervention. To address this knowledge gap, we have here detailed a study protocol that outlines a trial of two possible methods of scaling up this intervention: through centralized scaling and through decentralized (“train the trainers”) scaling where an external partner delivers the Shamiri intervention. This is one of the few ways to further increase the reach of the Shamiri intervention.

If this trial successfully demonstrates that the intervention maintains its utility irrespective of the implementation partner, it would provide valuable support for scaling up the intervention through an implementation partner, which would expand the reach of this low-cost meaningful and impactful intervention which can play a role in addressing the mental health treatment gap. This could mean an improvement of mental health for the adolescents themselves, but also an improvement for the school as a whole, by creating a positive learning environment and improving academic performance.

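### The stated 80% power is for intervention versus control and does not address the centralized-versus-decentralized comparison that one section names as primary

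*Protocol article*

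**What the plan says.** Sample size {14} takes its target from a contrast with control: "We used the lowest standardized effect size between the intervention and control we observed in a prior study" served "as our target effects, which was 0.22". At a significance level of 0.05 and at least 80% power, "an effective sample size (i.e., including attrition of 40%) of 1554 participants is required". Expected losses are "up to 30% attrition at the midpoint and endpoint and up to 40% by follow-up". Then: "We rounded this up to 1600 participants required at baseline". The article gives no other power figure and refers to supplementary materials for the details.

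The sections that state the aim differ:

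- **Explanation for the choice of comparators {6b}:** "The primary objective of this trial is to compare a centralized vs decentralized approach to scaling". Treatment as usual (TAU) is there as a reference point. The abstract and Trial design {8} frame the trial in the same way.
- **Objectives {7}:** the primary objective is broader, namely exploring ways to scale the intervention. Effectiveness is the first specific objective and is tied to the 1600 adolescents. The comparison of the two strategies is second, with the hypothesis that partner delivery is equally effective.

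The decision rule in Statistical methods {20a} judges the centralized and decentralized arms against control only. The Discussion looks ahead to a favourable result: "If this trial successfully demonstrates that the intervention maintains its utility irrespective of the implementation partner", it would support scale-up through a partner.

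**The concern.** A power figure belongs to one contrast and one size of difference. Here it is a Shamiri arm against TAU at 0.22 SD. The comparison that {6b} calls primary sets two implementers of the same manual against each other, and the hypothesis for it is equality. Two things do not carry over.

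First, 0.22 is the whole assumed benefit over control. A partner that lost 0.22 would do no better than TAU, so a shortfall worth worrying about would normally be some fraction of 0.22. Second, power to detect a difference does not show how well a trial can support the absence of one. That depends on the width of the confidence interval for the difference.

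At stake is the statement about equal effectiveness. If the interval is wide relative to 0.22, a non-significant difference between the Shamiri arms is the likely result even when the partner has lost half the benefit.

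**Working it through.** **Inputs from the protocol article.** Target effect 0.22; alpha 0.05 (taken as two-sided; the article does not say); power 80%; 1554 required and 1600 planned; losses of 30% at endpoint and 40% at follow-up (Sample size {14}). Equal arms (Sequence generation {16a}). Groups of 10 to 15 (Eligibility criteria {10}), midpoint 12.5.

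**Assumptions, not in the article.** SD 1; a single time point; group ICC 0 or 0.05; baseline-to-outcome correlation r of 0 or 0.5.

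**Step 1. The plan's own figure.** n per arm = 2 × ((1.96 + 0.84)/0.22)² = 325 after rounding up. Three arms: 975. With 40% loss: 975/0.60 = 1625, against the stated 1554. In reverse, 1554 × 0.60/3 = 310.8 per arm, SE = √(2/310.8) = 0.0802, power for 0.22 = Φ(0.22/0.0802 − 1.96) = 78.3%. The closed form does not return 1554 exactly, but it lies close to a pairwise test of one arm against another at 0.22. The stated figure came from a mixed-model simulation whose settings are not shown, so this gap does not show that 1554 is wrong.

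**Step 2. Centralized versus decentralized at 1600.**

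- n per arm: 1600/3 × 0.60 = 320 at follow-up; 1600/3 × 0.70 = 373 at endpoint.
- Design effect (DEFF) at ICC 0.05: follow-up 1 + (12.5 × 0.6 − 1) × 0.05 = 1.325; endpoint 1 + (12.5 × 0.7 − 1) × 0.05 = 1.3875.
- SE = √(2 × DEFF/n) × √(1 − r²), where √(1 − 0.5²) = 0.866.
- Half-width = 1.96 × SE. Detectable difference at 80% power = 2.80 × SE. Power for 0.11 = Φ(0.11/SE − 1.96).

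| Time | ICC | r | SE | 95% CI half-width | Detectable difference | Power for 0.11 |
|---|---|---|---|---|---|---|
| Follow-up | 0 | 0 | 0.0791 | 0.155 | 0.22 | 28% |
| Follow-up | 0.05 | 0 | 0.0910 | 0.178 | 0.26 | 23% |
| Follow-up | 0 | 0.5 | 0.0685 | 0.134 | 0.19 | 36% |
| Follow-up | 0.05 | 0.5 | 0.0788 | 0.154 | 0.22 | 29% |
| Endpoint | 0 | 0 | 0.0732 | 0.143 | 0.20 | 32% |
| Endpoint | 0.05 | 0 | 0.0862 | 0.169 | 0.24 | 25% |
| Endpoint | 0 | 0.5 | 0.0634 | 0.124 | 0.18 | 41% |
| Endpoint | 0.05 | 0.5 | 0.0747 | 0.146 | 0.21 | 31% |

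**Step 3. Reading the table.** Every half-width lies between 0.11 and 0.22. If the two arms are truly equal, an interval centred on zero excludes a loss of the whole target effect but not a loss of half of it. If the partner has truly lost 0.11, the difference is non-significant in 59% to 77% of trials (100% minus the last column).

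**The case against.** **Objectives {7} puts effectiveness first and links it to the 1600.** This stands. The stated size serves that objective, so a reader should not infer that the sample size is wrong or aimed at the wrong question altogether. The conflict is between Objectives {7} and section {6b}, and the stated power answers only one side of it.

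**The Discussion does not say that a non-significant difference would count as support.** This also stands. Retained utility with a partner can be read as each delivery arm beating TAU, which is what the decision rule tests. It would be too strong to say that the plan treats non-significance as evidence of equality. But two arms that each beat TAU can still differ by half the effect, so that reading does not establish the hypothesis of equal effectiveness either.

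**The trial is not limited to detecting complete failure of the partner.** A reader might infer this from the unadjusted 0.22. With baseline adjustment and no clustering the detectable difference is 0.19 at follow-up and 0.18 at endpoint, so that reading fails.

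**Clustering need not set the two contrasts apart.** At ICC 0.05, power for a 0.22 difference at follow-up is 68% between the Shamiri arms. Against TAU it is 73%, but only if TAU is unclustered. The allocation sections describe group numbers and leaders without exempting TAU, so nothing here rests on that gap.

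**The supplement may hold the second calculation, and the closed form is cruder than a repeated-measures model.** Both are possible. The supplement would not change the stated basis of the 0.22; if it holds the figure, reporting it takes one sentence. The crudeness is the reason to re-run the simulation and not to adopt the table above.

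**The article says openly that the effect is against control.** True, but it does not say that the comparison named as primary in {6b} is left without a figure.

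**Conclusion.** The point holds in this form: the only stated power concerns a Shamiri arm against control, it fits the first specific objective, and it does not address the equal-effectiveness hypothesis attached to the comparison that {6b} names as primary. For that comparison at follow-up the 95% confidence interval half-width is about 0.155 SD without clustering and 0.18 SD at ICC 0.05, or 0.13 to 0.15 SD with a baseline correlation of 0.5. Power to see a loss of 0.11 is about 23% to 36% at follow-up and 25% to 41% at endpoint. A non-significant difference would therefore not support equal effectiveness.

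The exact values rest on equal arms, the stated maximum losses, a single time point, and an ICC and correlation that the article does not give. The conclusion does not depend on clustering: with an ICC of zero and the favourable correlation, power for 0.11 is still at most 41%.

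**What to change.** 1. Reconcile Objectives {7} with section {6b} on which comparison is primary.
2. In Sample size {14}, state that 1554/1600 and 80% power apply to a Shamiri arm versus TAU.
3. Re-run the existing simr model for centralized versus decentralized delivery at 1600, with group clustering in both Shamiri arms and the 30% and 40% losses. Report the detectable difference and the expected 95% confidence interval half-width.
4. Base any statement that partner delivery is equally effective on the confidence interval for that contrast, not on a non-significant difference and not on each arm separately beating TAU. Word the corresponding Discussion sentence to match.

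The cost is one simulation run and a few sentences. Enrolment does not change; Trial status reports recruitment as complete. The downside is that the figure reported for the comparison named as primary will look less favourable than 80%.
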